## Abstract

**Background:**

Malaria remains a major health problem, especially in sub-Saharan Africa where more than 90% of the disease and where nearly all deaths occur in children. Adding to this high burden is the co-existence of intestinal and genito-urinary helminth infections. Existing control programmes for these helminths are operating sub-optimally. Conversely, a malaria prevention programme, called seasonal malaria chemoprevention (SMC), introduced in 2012 has achieved more than 75% treatment coverage and prevented 75–85% cases of uncomplicated and severe malaria in children. This encouraging development supports the need to explore strategies involving the integration of helminth control with successful platforms such as SMC. This would align worm and malaria control within the Sustainable Development Goals of ending the diseases of poverty and promoting health and well-being for those at risk.

**Methods:**

This study will have quantitative and qualitative components. The quantitative component will be a three-arm, observer-blind, placebo-controlled, interventional study of co-administration of SMC and anthelminthic drugs to pre-school and school-age children in Saraya district, southeast Senegal. Six hundred children aged 1–14 years will be randomly assigned to receive either SMC drugs only, SMC drugs and praziquantel or SMC drugs and albendazole and praziquantel at a ratio of 1:1:1. The primary outcome will be solicited and unsolicited adverse reactions to the study medications. The secondary outcomes will be the prevalence and intensity of *Plasmodium*-helminth co-infection and the prevalence of anaemia and mean haemoglobin concentration.

The qualitative component of the study will include the conduct of structured interviews to assess the acceptability, feasibility, enablers and barriers to the combined use of anthelminthic and SMC drugs among randomly selected parents/caregivers of children enrolled in the study and health care workers responsible for the delivery of the combined services.

**Discussion:**

This study will provide evidence to boost the public health recommendations for combined malaria and helminth control. If successful, this project will reinforce the evidence that health care systems in developing countries can be comprehensive health management rather than focussed on vertical management of a single disease.

**Trial registration:**

ClinicalTrials.gov NCT05354258. Registered on 28 April 2022. PACTR202204794105273. Registered on 25 April 2022

## Administrative information

Note: The numbers in curly brackets in this protocol refer to SPIRIT checklist item numbers. The order of the items has been modified to group similar items (see http://www.equator-network.org/reporting-guidelines/spirit-2013-statement-defining-standard-protocol-items-for-clinical-trials/).

## Introduction

### Background and rationale {6a}

Malaria and helminths frequently co-habit in children living in sub-Saharan Africa (SSA). An interplay of environmental and host factors favours mixed infections of malaria species with parasitic helminths including soil-transmitted helminths (STH) and *Schistosoma* species [1, 2]. Statistical and spatial models support the geographic overlap and co-endemicity of falciparum malaria and hookworm infections in SSA [3]. Similar spatial distribution studies have documented the association between malaria and schistosomiasis [4].

Despite the considerable progress that has been made in the control of malaria, SSA still account for an estimated 228 million cases in 2020, representing about 95% of global malaria cases [5]. Similar progress has been reported in the control of neglected tropical diseases (NTDs), chief among which are STH and schitosomiasis, which, however, still impose a major human, social and economic burden on more than 1 billion people globally, predominantly among vulnerable paediatric populations in SSA. It is estimated that 1.5 billion individuals are infected with helminths globally [6], with more than 800 million children in SSA affected by STH primarily hookworm (*Ancylostoma duodenale* and *Necator americanus*), roundworm (*Ascaris lumbricoides*) and whipworm (*Trichuris trichiura*) [7]. Other important helminths that co-exist with malaria in children in SSA include *Schistosoma haematobium* and *S. mansoni* [8].

The geographical overlap in the co-endemicity of helminths and malaria parasites may result in synergistic or antagonistic interactions between helminths and malaria parasites [2, 9, 10]. There is some evidence that infections with *Schistosomes* and STH exert deleterious effects on the course and outcome of clinical malaria [3, 9]. Prominent among the clinical outcomes of malaria-helminth co-infections among children living in SSA is anaemia [11, 12] resulting from blood loss, haemolysis, inflammatory processes or splenic sequestration [13, 14]. The additive effects of malaria-helminth co-infection on haemoglobin concentration probably contribute significantly to mortality from malaria in children in SSA [11, 15]. Also, a substantial proportion of malaria mortality in children is linked to anaemia [16], while iron deficiency anaemia (IDA) induced by helminth infestations is associated with stunted growth, impaired cognitive development, poor school attendance and low academic performance [15, 16].

Given this context, it is important to develop a treatment approach that combines malaria and helminth control in an integrated framework that is safe, effective and easy to deliver. This study will investigate the feasibility and effectiveness of co-administration of anthelminthic and SMC drugs in a high-risk paediatric population living in a malaria-helminth co-endemic setting of Senegal, West Africa. This study is designed to test the hypothesis that co-administration of SMC and anthelminthic drugs will be safe and tolerated among children aged 1–14 years and that the incidence of side effects will not be significantly higher in children who receive the combined SMC and anthelminthic drugs than in those who receive SMC alone. The study will also seek to establish the extent to which combined administration of SMC and anthelminthic drugs will reduce the prevalence of anaemia, malaria and schistosomiasis compared to SMC administration alone.

Given that the feasibility of delivery and the effectiveness of an intervention may be influenced by its acceptability by end-users and other stakeholders, the perceptions of parents/caregivers of children enrolled in this study, SMC providers and programme managers will be explored to gain information on the acceptability, feasibility, barriers, enablers and practicalities of using the integrated SMC-anthelminthic approach.

Overall, this study may provide evidence to boost public health recommendations for combined malaria and helminth control. If successful, this project will reinforce the evidence that the future direction of health care systems in developing countries should be comprehensive rather than vertical management of a single disease.

### Objectives {7}

The primary objective of this study is to assess the safety and tolerability of concurrent administration of SMC and anthelminthic drugs among pre-school and school-aged children in Senegal. The secondary objective is to evaluate the effects of combined treatment with SMC and anthelminthic drugs on the prevalence of malaria, anaemia and helminth infections among pre-school and school-age children in Senegal. The qualitative component of this study will explore the perceptions of parents/caregivers of study children, SMC/NTD providers and programme managers about the acceptability, feasibility, barriers, enablers and practicalities of using the integrated SMC-anthelminthic approach.

### Trial design {8}

A non-inferiority trial design is adopted to demonstrate that integrated SMC and anthelminthic drug delivery will be safe and tolerated among the study participants and that the incidence of the side effects will not be significantly higher in the study participants who receive the combined SMC and anthelminthic drugs than in those who receive SMC drugs alone. The study will include quantitative and qualitative components. The quantitative component will be a three-arm, observer-blind, placebo-controlled, interventional study of concurrent administration of SMC and anthelminthic drugs to pre-school and school-age children in the Saraya district of Kedougou region, southeast Senegal (Fig. 1).

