### Outcomes {12}

#### Primary outcome

All solicited and unsolicited adverse events will be assessed for causal relationships to the study medications, for six consecutive days after the administration of anthelminthic drugs.

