### Participant timeline {13}

#### Sample size {14}

Haemoglobin (Hb) concentration was used to calculate the sample size. Given that the mean Hb concentration in the SMC alone group in a previous study [18] in the same population was 10.5 g/dl, we assumed a mean Hb concentration of 11.0 g/dl in the SMC + anthelminth arm and a SD of the Hb concentration of 1.5 g/dl. To detect a mean difference between the treatment arms of 0.5 g/dl with 90% power at a 95% level of statistical significance, a minimum of 189 children per treatment arm will be needed. Allowing for 10% loss to follow-up, approximately 200 children will be enrolled into each treatment arm.

Based on a recent survey conducted in the study site (unpublished data), we assumed that the prevalence of any malaria or helminth infection in the SMC group will be 30%, the prevalence of any malaria or helminth infection in the SMC + anthelminth arms will be 16% and the relative risk will be 0.53 (that is, 47% reduction in the SMC + anthelminth arms compared to the SMC alone group). A minimum sample size of 188 children was considered sufficient to give 90% power at 95% confidence interval and 5% level of precision. Adding 10% loss to follow-up, approximately 200 children will be needed for each treatment arm. Therefore, a total of 600 children aged 1–14 years will be enrolled and randomly assigned at a ratio of 1:1:1 into the control and the two intervention arms.

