### Statistical methods

#### Statistical methods for primary and secondary outcomes {20a}

Infection intensities of positive samples will be calculated as the geometric mean of parasites per microlitre of blood for and geometric mean of eggs per gram of faeces for *S. mansoni*. For *S. haematobium*, infection intensity will be calculated as geometric mean of eggs per 10ml of urine. For pre- and post-intervention time points, the chi-square test will be used to compare proportions (prevalence) of malaria infection and prevalence of anaemia between the intervention and control groups. Similarly, for each time point, the Student *t*-test will be used to compare geometric mean parasite counts and mean haemoglobin concentrations between the intervention and control groups. The repeated measures analysis of variance will be used to compare geometric mean parasite counts and mean haemoglobin concentrations where repeated measurements for pre- and post-intervention time points are compared. All statistical tests will be two-sided at a significance of alpha < 0.05.

Qualitative data will be managed by NVivo software version 12.0 and analysis will be done by initially coding the main themes that emerge from the transcribed texts. The themes will subsequently be sorted and collated into categories and sub-categories. Hypotheses and concepts will be developed inductively from the themes. The findings of the qualitative and quantitative data addressing similar concepts will be triangulated in the final report.

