A passive surveillance system will also be implemented during the subsequent SMC cycles to complement the system described above. All study participants presenting for admission through the outpatient or emergency departments of Saraya health centre and health posts in the study villages will be evaluated. During the hospitalisation, the participant’s course of illness will be monitored to capture the symptoms and signs indicative of a severe adverse event. A blood sample for the evaluation of malaria parasites will be taken for all children attending a clinic who are reported to have had a fever within 24 h of presentation or have a measured axillary temperature of ≥37.5°C. Other possible sources of fever will also be investigated. A malaria rapid diagnosis test (RDT) will be performed to guide immediate patient management.

The investigators will evaluate any safety information that is spontaneously reported by a study participant beyond the time frame specified in the protocol. The investigators will monitor and analyse the study data including all adverse events and clinical laboratory data as they become available and will make determinations regarding the severity of the adverse events and their relation to a study drug. The investigator or clinical designee will review both adverse drug reactions and other adverse events to ensure prompt and complete identification of all events that require expedited reporting as serious adverse events.

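### The non-inferiority safety claim is worded as a non-significant increase in side effects, and the sample size is not linked to that primary question

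*Protocol article*

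**What the plan says.** - **Framework.** Trial design {8}: "A non-inferiority trial design is adopted to demonstrate that integrated SMC and anthelminthic drug delivery will be safe and tolerated". The same sentence gives the criterion: "the incidence of the side effects will not be significantly higher in the study participants who receive the combined SMC and anthelminthic drugs" than in children given SMC alone. Background and rationale {6a} words the study hypothesis the same way: "the incidence of side effects will not be significantly higher in children who receive the combined SMC and anthelminthic drugs".
- **Primary outcome.** The Primary outcome section reads "All solicited and unsolicited adverse events will be assessed for causal relationships to the study medications", over six days after the anthelminthic dose. The abstract reads "The primary outcome will be solicited and unsolicited adverse reactions to the study medications".
- **Tests.** Statistical methods {20a}: "All statistical tests will be two-sided at a significance of alpha < 0.05". The section names tests for malaria infection, anaemia, parasite counts and haemoglobin. It names none for adverse events.
- **Size.** Sample size {14}: "Haemoglobin (Hb) concentration was used to calculate the sample size". The inputs are a difference of 0.5 g/dl, SD 1.5 g/dl and 90% power, giving 189 per arm. A second calculation, on any malaria or helminth infection (30% against 16%, 90% power), gives 188. Allowing for 10% loss, the section enrols about 200 per arm. Haemoglobin and infection are secondary outcomes under Outcomes {12}.
- **Timing.** Trial status says that recruitment was completed on 21 June 2022. Blinding {17a} says that the data analyst is not masked.

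**The concern.** A non-inferiority conclusion needs evidence that the excess of harm is smaller than a stated amount. The criterion in Trial design {8} and Background {6a} asks only that an increase not reach significance. Those are different claims. The first gets harder to support as data become sparse; the second gets easier.

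Safety is the primary objective, and the Discussion says that efficacy probably needs a larger study. Yet the only reasoning behind the sample size concerns efficacy. A reader therefore cannot tell how large an excess of side effects this trial could rule out. At stake is a statement that combined treatment is safe for children aged 1–14 years, intended to support public health recommendations, resting on a non-significant test.

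**Working it through.** **1. The plan's own sample sizes.** Both are superiority calculations, and neither contains a margin.

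- Haemoglobin: n = 2(1.960 + 1.282)² × 1.5² / 0.5² = 189.1 per arm. The article states 189; rounding up gives 190.
- Infection, pooled two-proportion formula with mean prevalence 0.23: n = [1.960√(2 × 0.23 × 0.77) + 1.282√(0.30 × 0.70 + 0.16 × 0.84)]² / 0.14² = 187.8, so 188, as stated.

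Neither uses an adverse-event rate or a tolerable excess.

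**2. How often a real excess would meet the stated criterion.** The documents give no adverse-event rate, so the control risks are assumptions. The test is also inferred: a pooled two-proportion z-test, two-sided 5%, 200 per arm.

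Power = Φ{[d√n − 1.960√(2p̄(1−p̄))] / √(p₁(1−p₁) + p₂(1−p₂))}, where d = p₂ − p₁ and p̄ is the mean of the two risks.

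For 20% against 30%: (0.10 × 14.142 − 1.960 × 0.6124) / 0.6083 = 0.352. Power is 64%, so the excess is non-significant in 36% of trials.

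| Assumed control risk | True +5 points: non-significant | True +10 points: non-significant |
|---|---|---|
| 5% | 52% | 8% |
| 10% | 67% | 20% |
| 20% | 78% | 36% |
| 30% | 81% | 45% |
| 40% | 83% | 48% |

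Halving the arms to 100 raises the 20%-against-30% figure from 36% to 63%. Under this criterion a weaker trial is more likely to succeed.

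**3. A result that would pass.** Take 40/200 (20%) against 56/200 (28%).

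- z = 0.08 / √(2 × 0.24 × 0.76 / 200) = 1.87, so the increase is not significant.
- Upper 95% limit of the excess = 0.08 + 1.96√[(0.20 × 0.80 + 0.28 × 0.72) / 200] = 16.3 points.

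The criterion is met while an excess of 16 points remains compatible with the data.

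**4. What 200 per arm could support.** With equal true risks p and one-sided 2.5%, margin = (1.960 + z_power) × √(2p(1−p)/200), where z_power is 0.842 for 80% and 1.282 for 90%.

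| Assumed risk | Margin at 80% power | Margin at 90% power |
|---|---|---|
| 5% | 6.1 points | 7.1 points |
| 10% | 8.4 points | 9.7 points |
| 20% | 11.2 points | 13.0 points |
| 30% | 12.8 points | 14.9 points |

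Read the other way, power for a 10-point margin is 92% at 10% risk, 71% at 20%, 59% at 30% and 53% at 40%. With 180 per arm the figure at 10% risk falls from 92% to 89%.

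**The case against.** **The test is inferred.** Statistical methods {20a} names no adverse-event test, and a two-sided 5% level is compatible with reading a two-sided 95% confidence interval against a margin. This stands: the difference test is a reading of the criterion together with the general rule on tests. The criterion itself is stated twice, however, and a margin-based analysis elsewhere would contradict both statements.

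**A margin may exist in a document not shown.** The article rests on protocol version 2.0, and an analysis plan may exist. This also stands, so the absence of a margin from the article is not the charge. The charge is the criterion that the article does state.

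**The trial may be large enough.** It may. With a 10-point margin and a control risk of 10% or less, 200 per arm gives at least about 92% power. A reader might infer that the trial cannot answer its safety question. The documents do not support that: the same data yield a risk difference and its interval whatever the criterion says.

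**Two stronger readings go too far.**

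- One is that the trial has two competing primary endpoints, because the abstract speaks of reactions and the Outcomes section of events. Events assessed for causality yield reactions, so this may be loose terminology.
- The other is that causality is judged unblinded. Adverse event reporting {22} says that the investigators "will make determinations regarding the severity of the adverse events and their relation to a study drug", but not that they know the arm. Blinding {17a} blinds the staff who perform the safety assessments. The text leaves open whether the investigators fall within that blinding.

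**Conclusion.** The point holds for the decision rule and for the sizing. As written, the criterion for the declared non-inferiority claim is failure to reject equality, which cannot establish non-inferiority. The sample size is not tied to the primary outcome.

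The figures rest on assumed control risks of 5% to 40%, 200 analysed per arm and a pooled z-test. Over that range the stated criterion would pass a true 5-point excess more often than not. It would pass a true 10-point excess in about one trial in twelve at the lowest risk and nearly one in two at the highest. Whether 200 per arm is adequate depends on a margin and a control risk that the article does not give. The wording should be corrected before the safety result is interpreted; the endpoint terminology is minor.

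**What to change.** 1. **Criterion.** In Background {6a} and Trial design {8}, replace the non-significance wording. For each anthelminthic arm against SMC alone, conclude non-inferiority only if the upper limit of the two-sided 95% confidence interval for the risk difference, in children with at least one primary safety event, lies below the margin.
2. **Margin.** Justify it on clinical or external grounds, not from the available sample size. Fix, date and document it before any comparison by arm. Recruitment closed on 21 June 2022 and the safety window is six days, so these data were due within about a week of that date, and the analyst is unmasked. If arm-level data have already been seen, disclose this and report the risk difference with its interval, without a non-inferiority claim.
3. **Sample size {14}.** Say that both calculations concern secondary outcomes. State the power of about 200 per arm for the chosen margin over a range of control risks. Use about 180 if the 10% loss also applies to the six-day window.
4. **Terminology.** Use one term for the primary outcome in the abstract and the Outcomes section. Reporting all events irrespective of attributed causality, alongside related events, would be a sensible sensitivity analysis; it is not a required change of endpoint.

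The cost is a wording amendment and one documented margin decision, with no extra children or data collection. If the margin comes too late, the cost is giving up the formal non-inferiority claim.

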**Fig. 1 Fig1:**
[figure not shown]
Map of Senegal showing the study site. Source: https://www.cia.gov/resources/map/senegal/. Terms of use: https://www.cia.gov/site-policies

In June 2021, prior to the start of the malaria transmission season and before SMC administration commenced, we conducted a population-based survey to estimate the prevalence of malaria-helminth co-infections among children aged 1–14 years in 18 villages in Saraya district. Preliminary findings of this survey showed that the prevalence of malaria ranged between communities from 3.3 to 9.5% and of *Schistosome* infection from 12.2 to 64.8% (unpublished data). These findings will guide the selection of the villages for implementing the study described in this protocol. The schematic diagram of the study design is illustrated in Fig. 2.

**Fig. 2 Fig2:**
[figure not shown]
Schematic diagram of the study design: A day before the commencement of the first cycle of SMC, 600 eligible children aged 1–14 years will be randomly assigned to one of three arms at a ratio of 1:1:1 to determine the safety, feasibility and tolerability of the SMC and anthelminthic drug co-administration. The first group will receive vitamin A and zinc supplement and the second group will receive praziquantel and vitamin A while the third group will receive albendazole and praziquantel. On the following day, corresponding to the start (day 1) of the first SMC cycle, all the three groups will receive amodiaquine (AQ) and sulphadoxine/pyrimethamine (SP) according to the WHO and Senegal SMC implementation guidelines. On the second and third day of the SMC cycle, all study children in the three groups will receive AQ, in line with the SMC guidelines

The qualitative component of the study will involve the conduct of structured interviews to assess the acceptability, feasibility, enablers and barriers to the combined use of anthelminthic and SMC drugs among randomly selected parents/caregivers of children enrolled in the study. Key informant interviews will also be held with SMC and MDA (anthelminthic) providers as well as with the SMC and NTD programme managers from the Senegal Ministry of Health to further explore these factors.

